### Recruitment

Umbrella organisations in the nursing home sector in Flanders will be asked to distribute a short informational form about the project and inclusion criteria among their members. If nursing homes express their interest, the researchers (JG and [name]) will contact them by telephone to introduce the research, do a first check of eligibility, and plan a face-to-face introductory meeting on site. During this meeting, the researchers will inform facility management and head nurse(s) about the study procedures and formally evaluate all inclusion and exclusion criteria. Within two weeks the nursing home’s management will be asked to confirm agreement to participate by signing an agreement form prior to randomisation. In case a facility manager declines to participate, another one fulfilling the eligibility criteria will be selected until a sufficient number of nursing homes are recruited. If this recruitment strategy delivers insufficient nursing homes, the researchers will randomly call a sample of eligible nursing homes from the list of formally acknowledged nursing homes by the national health insurance administration (National Institute for Health and Disability Insurance, in Dutch: Rijksinstituut voor Ziekte- en Invaliditeitsverzekering - RIZIV, in French: Institut National d’Assurance Maladie-Invalidité - INAMI).

### Assignment of interventions

#### Randomisation

After the purposive identification of all nursing homes taking part in the study, they will be matched into pairs (1:1) and one of each pair will then be randomly assigned to the control or intervention group. Facilities that expressed to be interested to participate, are ordered (on a first come first serve basis) on a list which described their region, number of beds and facility type (non-profit, for-profit public/private). We contacted the nursing homes consecutively, starting with the first of the list. After we visited the nursing home, the eligibility assessment was made (using the eligibility criteria). If the nursing home was included, the next on the list was contacted unless there were already sufficient eligible nursing homes in a stratum, in which case the nursing home was skipped and another nursing home with different characteristics was contacted first. Paired randomisation will be performed by an independent and blinded statistician of Vrije Universiteit Brussel (VUB) via computer generated random numbers. The researchers will make a list of all included numbered, including information about facility status (public vs. private without profit objective vs. private with profit objective), location (province within Flanders) and number of beds. The nursing homes will be divided into groups; nursing homes from the same region are grouped. Within each group, nursing homes are subsequently subdivided to match in facility status and then number of beds. The randomisation procedure will be repeated if the numbers of beds are unbalanced i.e. if the difference between the control and intervention groups is greater than 15% of the largest group. Because we will include nursing homes with > 100 beds the difference will not be very great. The randomisation procedure will be repeated a maximum of three times; if an imbalance persists, the last randomisation result will be used for the study. In cases where nursing home staff in the control facilities receive training regarding ACP and/or initiate ACP with residents or families during the study period, these nursing homes will remain part of the control group as this can be part of standard best practice nursing home care. However, to have an extensive ACP policy and practice is an exclusion criterion for nursing homes to be included in the study. This based on the judgement of the two researchers (JG and [name]), using a list of 12 predefined criteria that define extensive policy and practice. This list is based on a list (of yes/no questions) which is used in a previous Flemish study [32]. Questions range from “The nursing home has a clear and written ACP policy”; “There is oral/written information made available to residents and family regarding ACP, ADs and the assignment of legal representatives” to “Wishes regarding the end-of-life for all nursing home residents (and/or their loved ones) are regularly discussed in team meetings, especially when there are changes”.

#### Blinding (masking)

The nature of the intervention makes it impossible to blind study participants because all those in the intervention group will receive additional training or information. During data collection, the researchers cannot be blinded because they will observe training sessions and conduct interviews with staff as part of the process evaluation, hence will know the staff who work in intervention facilities. The process evaluation will only be conducted in intervention facilities. During data analysis, researchers and statistician will be blinded for the unit of randomisation of each nursing home, using encrypted data.

### Data collection, management and analysis

#### Data collection methods

In each facility, a key contact person (facility manager, head of care, head nurse or quality coordinator) will be identified. After randomisation, this key contact person will fill in the questionnaire concerning the baseline structural facility-level characteristics. In addition, the contact person lists *all* eligible nursing home staff and volunteers. Each eligible staff member/volunteer will be assigned an anonymous code, which will enable the research team to link T0 to T1 data. As part of baseline and post-assessment, they receive a structured self-report questionnaire with his/her personal code. They will put the questionnaire in sealed envelopes and deposit it in a locked letter box (only accessible to the researchers) in a central spot in the nursing home. As was done in a previous Flemish and EU study, two reminders will be sent [19, 32]. Using the anonymous codes, the researchers will register response. For non-responders, the contact person of the nursing homes will be asked to re-distribute the questionnaire to this professional and send out a general reminder. These procedures are repeated eight months after baseline measurement. Newly hired staff and new volunteers are added to the list of codes and will also receive a questionnaire.

Data collection procedures for the process evaluation, described in detail in Table 3, are the following:
*structured diary of ACP Trainers:* the ACP Trainers keep track of all activities they perform regarding the ACP+ programme by filling in a structured diary on a weekly basis. The diary will be provided by JG via Google Forms, which will be password-protected and stored in a secured folder.*notes of ACP Trainers:* after each visit to a nursing home, trainers are asked to write a short report to the Trial Monitor (LP) via e-mail. These reports are held in a secured folder.*semi-structured individual interviews with ACP Trainers:* both trainers will be interviewed (60 to 180 min) by one of the researchers at four and eight months. They will be asked for verbal consent to audiotape the interview.*attendance lists:* at the beginning of every training or information session an attendance list will circulate among those attending and they will be asked to write down their name and signature. The key contact persons keep the lists in a secure place and will only hand over the total number of participants per session to the researchers.*observation of training sessions:* during the two-day training of ACP Reference Persons, the two researchers independently observe the training session using a structured observation checklist.*post-training survey:* all staff involved in a training session of the ACP+ programme receive an evaluation questionnaire about the quality of the training and trainer. The surveys will be handed out to the participants at the end of the training by the trainer. Participants will put the survey in a sealed envelope which is then put into the locked box, posted via mail or collected by the key contact person and handed over to one of the researchers. Surveys are anonymised.*semi-structured post-ACP interviews with residents and family:* via the key contact person and ACP Reference Persons of each intervention nursing home, at least three residentsand their families are recruited to engage in a semi-structured interview with one of the researchers. After an ACP conversation the staff will ask the resident, family or dyad if they would be willing to participate in an interview. If they respond positively, a date will be planned (preferably shortly after the ACP conversation). At the start of the interview, the researcher will go over the informed consent procedure with the resident and/or their family member. Interviews will last approximately 30 min.*semi-structured individual interview with management:* after the intervention, one member of the nursing home management per intervention nursing home will be invited by the researchers for a 30-min interview. The interview will be held in the nursing home and conducted by one of the researchers. Prior to the start of the interview informed consent will be asked and signed.*semi-structured group interview with ACP Reference persons:* after the intervention, at least two ACP Reference Persons per intervention nursing home will be invited by the researchers for a 60-min group interview. The interview will be held in the nursing home and conducted by one of the researchers. Prior to the start of the interview informed consent will be requested and signed for.*focus groups with nursing home staff:* after the intervention, six to eight staff members per intervention nursing home will be recruited via the key contact person to participate in a 30 to 60-min focus group, held in the nursing home and conducted by one of the researchers. Prior to the start of the interview informed consent will be requested and signed for.

All interviews and focus groups are structured according to a prespecified topic list and audio-taped for analysis purposes. These will all be conducted by JG and [name].

#### Data management

Data will be entered as soon as possible after receipt of each questionnaire in a secure open source web-based survey application (Lime Survey). All paper forms, including written informed consent files and questionnaires, are stored in a lockable filing cabinet in a room with restricted access on campus. The participating nursing homes’ names, address and other identifying information will be stored in one file only. This file will be restricted to a few members of the research team (JG, LP, [name] and [name]). Consistent with the Good Clinical Practice (GCP) guidelines, the data (without information that is confidential, privacy-sensitive or that could identify individual people) and informed consent files will be stored for 15 years. Other documentation such as potential logbooks of the analyses, published papers, relevant e-mail correspondence etc. will be handed over in digital format to the project lead ([name]). In case data is shared, a secure method will be used, to ensure it cannot be accessed by anyone outside the research team. This includes email using a suitable encryption programme, with the password sent by another method (usually telephone) or post in a secure envelope.

#### Analysis

##### Outcome analysis

We will calculate summative scale scores for both primary and secondary outcomes. The resulting scale score for an individual is the sum of the individual item scores. For the knowledge items instructions are provided to check correct answers. If people answered, ‘I don’t know’, this will be scored as an incorrect item. The summative scale score of knowledge is sum correct knowledge items of 11 correct/incorrect answers. The summative scale score of ‘self-efficacy’ is the sum of self-efficacy items on a 10-point scale, ranging from 1 to 10, with 12 items. The primary statistical analyses will use an intention-to-treat (ITT) approach. In ITT the outcome data from all of the samples who were enrolled and randomised to the intervention or control group will be accounted for in the main analyses in the original groups to which they were randomised, regardless of whether or not they completed the ACP+ programme. We will fit a linear mixed model with condition, time and time*condition as fixed factors and with a random intercept for nursing home pair, random slope for time, condition and time*condition at the level of nursing home pair, random intercept for member, random slope for time at the level of member. The need for random slopes will be tested by comparing the difference between − 2 log (max) REML likelihoods with a $$ {\chi}_{1:2}^2 $$ distribution (using a mixture of chi-square distributions). In case of convergence issues, random slopes will also be left out of the model. Estimated cluster-adjusted means with corresponding 95% CI will be reported at T0 and T1, both for the intervention and control group. Differences in mean change (post- measurements minus baseline) between the intervention group and the control group (interaction group*time) will be calculated. All analyses will be two-tailed and considered significant if α = 0.025. Data will be analysed in SAS, R and IBM SPSS.

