### Study population and respondents

#### Nursing home staff and volunteers

Both the intervention and data collection methods are targeted at multiple staff members and volunteers working in the nursing home. Nursing home staff are people employed by the nursing home and include two groups:
nursing home ‘care’ staff are nurses, care assistants, psychologists, physiotherapists, occupational therapists, social workers, animators, pastoral or spiritual caregivers, moral consultants, reference persons for dementia or reference persons for palliative carenursing home ‘support’ staff are staff working in the nursing home but without having a role in care provision i.e. cleaning, administrative, technical/logistical or kitchen staff who have regular contact with residents or family but do not provide direct care to them.

Nursing home staff are included if they are able to speak and understand Dutch. Volunteers are included if they are registered at the nursing home and able to speak and understand Dutch. Students, interns or volunteers under 18 years old are excluded from participation.

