### Outcomes

#### Primary outcome

The two primary outcomes are: 1) nursing home care staff’s knowledge of ACP and 2) nursing home care staff’s confidence in their own skills regarding ACP (self-efficacy). These outcomes are measured at baseline (T0) and after eight months (T1). We assess knowledge and self-efficacy as these are identified as necessary intermediate steps for healthcare professionals to be able to actually engage in ACP, according to both social cognitive theory and literature about successful ACP [9, 10, 27].

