#### Outcome measurements

To evaluate ACP knowledge, attitudes, self-efficacy and practices, we developed a questionnaire, based on the questionnaire in a study from Detering et al. [28], which was translated via forward-backward translation and adapted to fit the local context. Items were added based on the Questionnaire Tool for Registered managers from Ulster University [29] and expertise of the multidisciplinary author group. The adapted version of the questionnaire was tested with six researchers who have clinical practice experience with older patients (three registered nurses, one GP, one psychologist and a nursing home volunteer), and through an online survey with 107 healthcare professionals and volunteers active in the Flemish nursing home setting. All items were reviewed and discussed within the author group and questions related to legal issues were additionally reviewed by an expert in Medical Law. Results of this trial will be based on the final version of the questionnaire (Additional file 1).

In the knowledge section of the final version of this questionnaire, respondents are asked to respond to 11 statements (e.g. ‘a nursing home resident can only assign a family member to be his/her legal representative’) ‘true’, ‘false’ or ‘I don’t know’. The self-efficacy section asks respondents to indicate how confident they feel (10-point Likert scale, ranging from ‘little confidence’ = 0 to ‘a lot of confidence’=10 and ‘not applicable’) regarding 12 items (e.g. ‘how confident do you feel about: initiating ACP conversations?’). In the attitudes section respondents are asked to indicate how strongly they agree or disagree (5-point Likert scale ranging from ‘completely disagree’ = 0 to ‘completely agree’ = 5) with 12 statements (e.g. ‘in most cases nursing homes residents do not know enough about healthcare to construct an advance directive’). The construct ACP practices asks about ACP activities in the past six months (e.g. initiating an ACP conversation, drafting of an advance directive, etc). For support staff and volunteers the ‘self-efficacy’ and ‘ACP practices’ sections are adapted to include three items evaluating ‘self-efficacy’ and two items to evaluate ‘ACP practices’. These items are all based on the main questionnaire. Table 2 provides a full overview of outcomes and measures. Questions and scale metrics of the measures are provided in Additional file 1.

**Table 2 Tab2:** Outcomes and outcome measures of ACP+ trial

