	Volunteer	7 items	Age, gender, date of today, employment status, highest education, number of years active as volunteer, number of years active as volunteer in this nursing home
Structural facility-level characteristics	Key contact person in nursing home	21 items	Type of facility, number of beds recognized by government, number of beds available, number of beds occupied, number of residents per KATZ scale category, umbrella organisation, with which electronic resident file system they work (e.g. GERACC, Care Solutions or others), number of residents died over past six months, average time of stay, availability of specific written guidelines available about palliative care or ACP, availability of patient-specific forms regarding ACP, % of residents died in nursing home, % of residents that has an up-to-date plan regarding end-of-life care, number of residents with written AD, regular multidisciplinary team meetings, number of staff: FTE and heads, number of volunteers registered in nursing home, number of hours per week the coordinating advisory physician is present in facility, number of GPs involved with patients in nursing home

*ACP* advance care planning; *GP* general practitioner; *FTE* full-time equivalent; *AD* advance directive; *KATZ* index of independence in activities in daily living; *GERACC* software package for nursing homes in Belgium

*Response categories: ‘True’, ‘False’ or ‘I don’t know’

†Response categories: 10-point Likert scale, ranging from ‘little confidence’ (=0) to ‘a lot of confidence’ (=10) and ‘not applicable’

‡Response categories: 5-point Likert scale ranging from ‘Completely disagree’ (=0) to ‘Completely agree’ (=5)

§Response categories: ‘Yes’ or ‘No’

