### Trial monitoring

The researchers will continuously monitor responses using MS Excel sheets. A Trial Monitor (LP), will be put in place to monitor, together with the research team, the course of the trial. She will act to oversee the progress of the trial and to ensure it will be conducted in accordance with the protocol and GCP [34]. She will also function as main contact person for participating nursing homes to report problems or to ask questions regarding the trial. All data entry will be performed by paid student(s) who are not involved in the research and hired to perform data entry alone. Data will be entered as soon as possible after receipt of each questionnaire in Lime Survey. The Trial Monitor will be responsible for checking and merging trial data. Independent double data entry will be required for 10% of the data to assess accuracy and to avoid data typing or editing errors. We will follow the guidelines of the EMGO’s (Scientific Quality Committee Amsterdam) Quality Handbook regarding data entry accuracy [52]. After data entry, a second database will be created into which a random sample of questionnaires (selected by LP) can be re-entered. The data entry programme identifies double data entry when the second entry is completed correctly. In addition, the researchers (JG or [name]) will check for and delete duplicate data entries after all data have been entered. If the number of errors on any given questionnaire exceeds 3%, the entire questionnaire must be re-entered. With regard to handling missing data, researchers will register the anonymous code (of eligible participants in the primary outcome measurement) for which no survey was received (MS Excel sheet). These codes will be signalled to the contact person who will be asked to send/present a reminder (i.e. the usual questionnaire). If forms have not been returned, up to two reminders are sent out.

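### The self-efficacy primary outcome is a raw 12-item sum although items can be answered 'not applicable', so the score also depends on how many items were rated; the item range is stated two ways

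*Protocol article*

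**What the plan says.** Self-efficacy is one of the two primary outcomes, described under Primary outcome as "nursing home care staff’s confidence in their own skills regarding ACP (self-efficacy".

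Under Outcome measurements its 12 items are answered on a "10-point Likert scale, ranging from ‘little confidence’ = 0 to ‘a lot of confidence’=10 and ‘not applicable". The Table 2 footnote repeats this: "10-point Likert scale, ranging from ‘little confidence’ (=0) to ‘a lot of confidence’ (=10) and ‘not applicable".

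Under Outcome analysis the general rule for every scale is: "The resulting scale score for an individual is the sum of the individual item scores". For self-efficacy the section adds that the score "is the sum of self-efficacy items on a 10-point scale, ranging from 1 to 10, with 12 items".

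The same section settles the non-substantive answer on the knowledge scale, where 'I don't know' "this will be scored as an incorrect item". It gives no matching rule for 'not applicable'. The missing-data text under Trial monitoring deals with codes "for which no survey was received", that is, with whole questionnaires and not with unrated items.

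**The concern.** A sum measures confidence only if everyone contributes the same items. Here an item marked 'not applicable' has no score, so under the literal rule it adds nothing. On a 0 to 10 item that equals the lowest confidence; on a 1 to 10 item it falls below the floor of the scale. If the whole sum were set to missing instead, scores would be lost according to job role.

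Item applicability probably differs between staff. The care-staff group includes "nurses, care assistants, psychologists, physiotherapists, occupational therapists, social workers, animators, pastoral or spiritual caregivers" and others. Randomisation should balance that on average at baseline, but not necessarily at eight months. ACP+ divides staff into Reference Persons, Conversation Facilitators and Antennas during the intervention period, and control homes receive no such role assignment. The number of items a person can rate may therefore change between T0 and T1 differently by arm, and the planned effect estimate is exactly the between-arm difference in change. At stake is whether an observed difference on a primary outcome reflects confidence or a change in which items staff regard as theirs.

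Separately, the two stated item ranges imply different score totals, so reported means could not be read against a known scale.

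**Working it through.** **The plan's own figure.** The only trial figure needed is the target effect of 0.5 in Sample size. To check its units:
- Design effect = 1 + ((0.17² + 1) × 30 − 1) × 0.036 = 2.075 (stated 2.07).
- Effective n per group = 161 / 2.07 = 77.8.
- Power for 0.5 SD at two-sided alpha 0.025, noncentral t with 2 × 77.8 − 2 degrees of freedom = 80.26% (stated 80.27%).

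So 0.5 is in SD units. The scoring point itself does not depend on the sample size.

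**Score range.**
- Items 0 to 10: total 12 × 0 to 12 × 10 = 0 to 120. This is an 11-point item, although it is called 10-point.
- Items 1 to 10: total 12 × 1 to 12 × 10 = 12 to 120.

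**Effect of unrated items on the literal sum (exact, no assumptions about SD).** A person who gives 7 to every applicable item scores 7 × k, where k is the number rated:

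| Items rated | Sum | Mean of rated items |
|---|---|---|
| 12 | 84 | 7 |
| 10 | 70 | 7 |
| 8 | 56 | 7 |
| 6 | 42 | 7 |

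The order of people can also reverse: full confidence on 8 applicable items gives 8 × 10 = 80, below the 84 of someone at 7 on all 12.

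**Possible shift in the arm contrast (illustration).** The protocol gives no SD and no 'not applicable' frequency. Assumptions: newly rated items score r = 6; SD of the sum is 24 (2 points per item × 12). Let p be the fraction of staff affected and d the change in rated items among them, both net of controls.

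Shift in SD units = p × d × r / SD

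- p = 1, d = 1: 1 × 1 × 6 / 24 = 0.25 SD.
- p = 0.20, d = 2: 0.20 × 2 × 6 / 24 = 0.10 SD.
- Range for p = 1, d = 1: from 5 / 30 = 0.17 SD to 7 / 18 = 0.39 SD, for r from 5 to 7 and SD from 18 to 30.

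The sign of d is not fixed by anything in the protocol.

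**Does a mean of rated items solve it completely?** No. Eight items at 7 give a mean of 7.0. If the person later also rates four harder items at 4, the mean becomes (56 + 16) / 12 = 6.0 with no loss of confidence on the original eight. The raw sum would move from 56 to 72 in the same case. The mean removes the dependence on the count, but not the dependence on which items are rated.

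**The case against.** **The rule may be elsewhere.** Scale metrics are said to be in Additional file 1, which is not shown, and handling of unrated items is often left to an analysis plan. 'Sum' can be read as naming the type of score, and a prorated or imputed total is also summative. This stands in part: the protocol does not say that 'not applicable' is coded 0. But it does fix a plain sum of item scores over 12 items that allow an unrated answer. A mean or prorated score elsewhere would depart from that text, and the range conflict lies wholly within it.

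**Direction.** A reader might infer that the score is inflated in favour of ACP+, because trained staff start rating items they used to skip. The document does not support this. Staff made Antennas recognise and pass on triggers, while others hold the planned conversations; such staff could mark more conversation items 'not applicable' at T1, which would lower a literal sum. This objection stands.

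**Size.** A reader might also take 0.25 SD as the trial's bias, or conclude that two switched items cancel the 0.5 target. Both are one-person shifts unless they are the average net change over the whole arm. This objection stands too.

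**Loss of respondents.** If sums with 'not applicable' items were set to missing, the linear mixed model could still use the person's other time point, so the loss is less complete than it looks. Bias would depend on missingness beyond what the model conditions on.

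**The range conflict.** Both arms receive the same questionnaire, so it cannot bias the comparison. The attitude scale shows the same pattern (5-point, yet 0 to 5), which suggests mislabelled anchors. Calling the scale uninterpretable would be too strong.

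**Conclusion.** The point holds as a fault in a stated scoring rule for a primary outcome. As written, the self-efficacy sum depends on the number of items rated (84 against 56 for the same uniform rating of 7 with 12 or 8 items), and that number can change by arm because role assignment is part of the intervention. It could bias the group-by-time effect. Neither direction nor size can be derived from the protocol; the shifts of 0.25 SD (average net change of one item per person) and 0.10 SD (net two items in 20% of staff) rest on an assumed rating of 6 and SD of 24. If 'not applicable' is rare, or changes equally in both arms, the effect on the contrast would be small.

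The conflict between 0 to 10 and 1 to 10 is a separate, lesser matter. It affects the reading of reported means only.

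**What to change.** - Score self-efficacy as the mean of the items rated, or equivalently the prorated 12-item sum, with a prespecified minimum number of rated items. The threshold is the trial team's choice.
- State that 'not applicable' is never scored 0.
- Report the number of 'not applicable' answers by arm and time point.
- Add a sensitivity analysis restricted to items that each person rated at both T0 and T1, because the mean can also shift when the set of rated items changes.
- Give one item range, matching the printed questionnaire, in Outcome measurements, Table 2 and Outcome analysis: 0 to 10 (total 0 to 120) or 1 to 10 (total 12 to 120).
- Apply the same rule to the three-item version for support staff and volunteers, which carries the same response options in Table 2.

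The cost is a change of wording before analysis, one extra descriptive table and one extra model; no new data are needed. The downsides are that some scores rest on fewer items, and that the sensitivity analysis excludes people without both time points.

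### The member-level random slope for time cannot be estimated from two visits, and the level-blind convergence rule lets that redundancy remove the pair-level slopes that protect the group-by-time test

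*Protocol article*

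**What the plan says.** All from the Protocol article.

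- **Visits** (Primary outcome): "These outcomes are measured at baseline (T0) and after eight months (T1"). Secondary outcomes follow the same schedule. No third visit or replicate score is described.
- **Member level** (Outcome analysis): "random intercept for member, random slope for time at the level of member", in addition to the residual of a linear mixed model.
- **Pair level** (same section): a random intercept for pair and a "random slope for time, condition and time*condition at the level of nursing home pair".
- **Selection rule** (same section): "The need for random slopes will be tested by comparing the difference between" REML -2 log-likelihoods, referred to a 1:2 chi-square "distribution (using a mixture of chi-square distributions").
- **Fallback** (same section): "In case of convergence issues, random slopes will also be left out of the model".
- **Staff seen once** (Data collection methods): "Newly hired staff and new volunteers are added to the list of codes and will also receive a questionnaire". Leavers contribute T0 only.
- **Level** (Outcome analysis): "All analyses will be two-tailed and considered significant if α = 0.025".

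**The concern.** A member has at most two scores. A member intercept variance, slope variance, intercept-slope covariance and residual variance are more than two scores can determine, at any sample size. Three things follow.

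1. The pre-specified primary model contains a redundant parameter by construction. Fitting trouble (a flat likelihood, a covariance matrix that is not positive definite) is therefore foreseeable and not a remote contingency.
2. The test that decides whether the member slope stays responds only to a difference in score variance between the visits, and it uses the wrong reference distribution.
3. The convergence sentence does not say which slopes go. Each pair holds one home per arm, so the pair-level time and time-by-condition slopes are the terms that carry variation between homes in change. If a member-level problem takes them out as well, the group-by-time test treats staff in one home as independent with respect to change.

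The third is what could reach the primary result.

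**Working it through.** **Inputs.** From Sample size: ICC 0.036, mean cluster size 30, coefficient of variation 0.17, 161 staff per group. From the Abstract: 14 homes, so 7 per arm and 161/7 = 23 staff per home. From Outcome analysis: two-sided level 0.025, critical z = 2.241. Assumed, because the article does not give them: within-member T0-T1 correlation r = 0.5 to 0.7, and correlation of home means over time (CAC) = 0.8 or 0.5.

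**The plan's own figure.** Design effect = 1 + ((1 + 0.17²)·30 - 1)·0.036 = 2.075 (stated 2.07). With 2.07, the noncentral t gives 80.26% power (stated 80.27%). It reproduces, and the point below does not depend on it.

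**Step 1: identifiability.** Code time 0/1. Let a = intercept variance, b = intercept-slope covariance, c = slope variance, s = residual variance.
- Var(T0) = a + s
- Cov(T0,T1) = a + b
- Var(T1) = a + 2b + c + s

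Four parameters map onto three moments. The Jacobian has rank 3, and moving (a, b, c, s) along (+1, -1, +2, -1) changes nothing observable. With both variances 1 and covariance 0.5, the pairs (s, c) = (0.5, 0), (0.3, 0.4), (0.1, 0.8) and (0.01, 0.98) all give the same matrix.

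Staff seen once inform only Var(T0) or Var(T1), so they do not help. In a simulated data set with 7 pairs, 14 homes, 23 members per home and about 25% of members seen once, -2 REML was 896.857038 for each of (s, c) = (1.0, 0), (0.7, 0.6), (0.4, 1.2) and (0.1, 1.8).

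If b were fixed at 0, c would be estimable, but only as Var(T1) - Var(T0), and it could not be negative. The 1:2 mixture is the reference for adding a slope variance together with its covariance, so it points to the correlated version.

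**Step 2: what the test tests.** For complete pairs with separate group-by-time means, the REML likelihood ratio between the models with and without the slope is -(N - 2)·log(1 - ρ²), where ρ is the correlation of a member's T0+T1 with T1-T0. This is the Pitman-Morgan test of Var(T0) = Var(T1), with a chi-square(1) reference. The mixture's 5% cut-off is 5.138, and P(chi-square(1) > 5.138) = 2.3%. At a 2.5% level the cut-off is 6.483 and the true size 1.1%.

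Simulation with 322 independent members, complete pairs and cut-off 5.138 (the 5% level is assumed; the article sets none specifically for this test):

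| Scenario | Slope kept |
|---|---|
| No slope, equal variances | 2.3% |
| True slope variance 0.4, equal variances | 2.3% |
| No slope, Var(T1) = 0.9, covariance 0.45 | 12% |
| No slope, Var(T1) = 0.7, covariance 0.45 | 93% |
| No slope, Var(T1) = 1.4, covariance 0.5 | 85% to 86% |

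**Step 3: effect of the member slope alone.** Comparing a member intercept only with the equivalent of intercept plus slope, in 322 independent members and 1,500 simulated trials per scenario:
- complete pairs: identical group-by-time estimates; mean standard error 0.0996 under both;
- 25% seen once and Var(T1) = 0.7: mean standard error 0.1107 against 0.1106; type I error 2.7% against 2.6% at nominal 2.5%.

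**Step 4: if every slope is dropped.** Variance of change between homes: h = 2·0.036·(1 - CAC). Within homes: w = 2·0.964·(1 - r). Variance inflation = (23h + w)/(h + w). Approximate type I error = 2·P(Z > 2.241/√inflation).

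| CAC | r | h | w | Inflation | Type I error |
|---|---|---|---|---|---|
| 0.8 | 0.5 | 0.0144 | 0.9640 | 1.324 | 5.1% |
| 0.8 | 0.7 | 0.0144 | 0.5784 | 1.534 | 7.0% |
| 0.5 | 0.5 | 0.0360 | 0.9640 | 1.792 | 9.4% |
| 0.5 | 0.7 | 0.0360 | 0.5784 | 2.289 | 13.8% |

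**The case against.** The strongest reply is that a redundant nuisance parameter does no harm. Step 3 bears this out while the pair-level slopes remain. Nor does the test lead to a poor marginal covariance: if the variances differ, keeping the slope lets the model fit them; if they are equal, dropping it leaves compound symmetry, which is then adequate. That part stands, so the member slope on its own is not a threat to the primary estimate.

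It is also fair that the inflation in Step 4 needs two further links: the redundant term must produce a reported convergence failure, and the analysts must then remove slopes at every level. Software may instead report convergence on a flat likelihood with an arbitrary split between slope and residual, and the rule would not fire. The pair-level structure can also fail by itself: four random effects, if unstructured, have 10 covariance parameters to be estimated from about 7 pairs. Loss of the pair slopes could therefore not be blamed on the member term alone. Both cautions stand.

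Finally, random slopes are already provisional in the plan, and parameterisation and fallback order are often left to an analysis plan. This answers less. The member slope, its reference distribution and a fallback without a level are all written into the article; they are not omissions.

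Two stronger readings are tempting. A reader might infer that the plan states a null hypothesis of no variation between members in change and tests something else; it states no such null, only that the need for slopes will be tested. A reader might also infer that a ceiling on the 11-item knowledge score would be reported as staff differing in their response; the article nowhere plans to report or interpret a member slope variance.

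**Conclusion.** The point holds in a limited form. In the correlated version that the mixture implies, the member slope variance is exactly unidentifiable, and its test is an equal-variance test with a true size of about 2.3% at the mixture's 5% cut-off. In the uncorrelated version the slope is only the difference between the two visit variances. Neither materially alters the group-by-time result while the pair-level slopes are kept.

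The consequence that matters is conditional on the convergence sentence being applied to all levels. Type I error would then rise from 2.5% to roughly 5% to 14%, depending on the assumed correlations. These are normal-approximation figures resting on the article's ICC of 0.036 carried over to home-level change through the assumed CAC. They show what the wording permits and do not predict what will happen. The change should be made before the analysis; the design itself is not in question.

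**What to change.** In Outcome analysis:

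1. Delete the member-level random slope for time and exclude the member level from the slope-testing rule. Model a member's two visits with an unstructured 2x2 covariance (variance at T0, variance at T1, covariance) in place of the member random effects. If this fails, use a member random intercept with visit-specific residual variances, then with a common residual variance.
2. Reword the convergence sentence so that simplification is confined to the level that fails. A member-level problem must not remove the pair-level time and time-by-condition terms. Because the pair level may have difficulties of its own, give it a separate simplification order.

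The cost is two sentences, settled before unblinding. No data or participants are added, and no estimable information is lost, because the deleted parameter could not be estimated from two visits.
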